### Overview of study design

The current study will use a hybrid type I effectiveness-implementation approach to test implementation of an EHR-derived suicide risk model to facilitate identification, recognition, and engagement in supportive suicide prevention services among individuals who are estimated to be at risk for suicide and receiving services in behavioral health clinics at the participating health systems. This includes a stepped wedge cluster randomized trial design [31, 32] with randomization of behavioral health clinics into three waves across the three participating health systems. This design offers a novel approach to studying service delivery interventions as it provides a baseline period without implementation followed by random and sequential crossover of clinics from usual care control to intervention until all participating clinics are exposed. All clinics will have a pre-implementation phase (baseline period). Within that, just prior to implementation, health systems will train clinicians. Clinician training materials will be provided but sites will operationalize the training according to local customs and resources. Differences in training rigor provide additional variability as they may partially account for acceptability or feasibility. Implementation begins when each randomized clinic (stratified by site) transitions from usual care to running the risk model so clinicians can observe the risk indicator (the intervention is the enhanced care model with the suicide risk model and associated clinician notification). Analyses will examine within and between clinic variation in outcomes and account for time since implementation. This design allows implementation of the intervention at all clinics during the study period, a requirement of our clinical stakeholders; similar designs have been used in other suicide prevention trials [33, 34].

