### Proposed care models (mechanisms of action)

Figure 3 shows a standard suicide prevention care model (usual care) and the proposed enhanced care suicide risk model (intervention). A typical workflow that involves suicide risk identification, when a patient presents for a behavioral health visit, may begin with suicide risk screening (typically the PHQ9 [42] in the participating sites). If the PHQ9 is missed, refused, or if item 9 (“Over the last two weeks, how often have you been bothered by thoughts that you would be better off dead or of hurting yourself in some way?”) is denied, the workflow may terminate, however a clinician could also proceed if clinically indicated. Potentially terminal processes are indicated by a dark background in Fig. 3, text boxes with white backgrounds indicate continuation of the workflow. The expectation is that when patients respond positively to item 9 (i.e., respond with a score of 2 “more than half the days” or 3 “nearly every day”), a comprehensive suicide risk assessment is conducted (typically the Columbia Suicide Severity Rating Scale [C-SSRS] [43] in the participating sites). Again, if the risk assessment is missed, refused, or if risk is denied the workflow may terminate. The expectation is that when risk is confirmed, depending on acuity, a referral is made to outpatient supportive services or to the emergency department or inpatient setting.

The enhanced care suicide risk model (intervention) demonstrates the proposed changes in workflow with the risk model implementation. In this model, the suicide risk model flags the clinician in the EHR to conduct additional suicide risk screening. The expectation is that if the PHQ9 were missed, refused, or if item 9 was denied in the presence of a model-generated risk flag indicating elevated estimated risk, then the clinician would proceed to the C-SSRS as if the screening were positive.

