### Sample size and power analysis

We anticipate including > 50 clinics and approximately 395,000 unique behavioral health patients across three sites over a 2.5-year period, leading to over 1 million patient visits. We project that approximately 4–5% of patients will be identified as high risk and thus eligible for the intervention. Utilizing a stepped-wedge cluster randomized controlled trial design, with > 50 clinics randomly assigned across three waves, we will assess the primary outcome, suicide attempts, at 90- and 180-days post-intervention. Given an anticipated suicide attempt rate of 0.6% (*n* = 2,370) within 90 days of a visit, a 0.01 intraclass correlation coefficient within waves, we expect to achieve more than 80% power (2-sided *p* <.05) to detect an effect size corresponding to a 1.5% absolute difference in suicide attempt rates [47–49].

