Generalized Linear Mixed Models (GLMMs) with logit link function will be used to assess categorical outcomes (identification and recognition, separately, defined as yes/no) to study the effect of the intervention on identification and recognition. The results will be presented as odds ratios (OR) with 95% CIs. We will analyze the frequency of events identified through PHQ-9 (identification), recognized through the C-SSRS (recognition), or both combined. Additionally, GLMMs with a log link function will be used to separately assess the effects on identification and recognition by modeling the count of identified or recognized patients. The model will include the intervention (yes/no) as an independent variable to assess its effect while accounting for clustering and potential confounders. Among visits where individuals are identified or recognized as being at risk, we will further investigate factors influencing these outcomes, including patient demographics and clinical characteristics. The results will be presented as relative risk (RR) with 95% CIs. In these analyses, clusters will be analyzed according to their randomized crossover time. Models will include a random effect for cluster and a fixed effect for each phase, and will adjust for age, sex, race/ethnicity and cluster/clinic terms (i.e., secular trend). These models are optimal and commonly used for studies implementing stepped wedge cluster randomized trial designs [31, 32, 50]. All analyses will also adjust for time, given that the ratio of exposed clinics increases over time, and calendar month to account for seasonality of suicide attempts. Given that patients may be screened or identified as at-risk multiple times, the frequency of visits during the follow-up period will be adjusted in the model as well. In additional analyses, the model will account for cluster effects by clinic and correlation between repeated measurements for the same patient over time.

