These models will also be used to test mediators/mechanisms, given that we hypothesize that identification alone will not reduce suicide outcomes but rather increase the number of people receiving suicide intervention, which could lead to improvement (i.e., decrease) in suicide outcomes. Mechanisms include interaction with the alert and initiation of assessment, which starts the outpatient care pathway. We will also stratify analyses by health system site, and test for mental health diagnoses and prior suicide attempts as moderators. Importantly, we will exclude ‘training’ months for each phase of clinic implementation from the main analyses, since clinicians and patients may be partially exposed as the models are implemented and clinicians trained. In a secondary set of analyses, we will explore potential heterogeneity in treatment effects between clinics. Here we will conduct additional analyses to test within cluster comparisons of exposed and unexposed periods.

To examine the effectiveness of a suicide risk model on health service engagement and suicide attempt outcomes, we will start with similar descriptive and GLMMs analyses proposed previously for identification and recognition. The analyses here will focus on each unique health service engagement (supportive and crisis encounters separately) and suicide attempt outcomes, stratified by exposed (intervention) versus unexposed (control) groups. Suicide attempts will be captured by health system records using ICD-10 diagnosis codes occurring within the same 90-day and 180-day time periods. We will also use a Kaplan-Meier method and Cox-proportional hazards models to examine time-to-event for health service engagement and suicide attempts, with statistical adjustment for clinical and demographic factors. Individuals will be censored at the time of death or at 180 days past the index visit. We will again add terms for calendar month as well as site to account for variation by season and health system.

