Finally, we will separately examine the impact of health care engagement and exposure to ZS evidence-based interventions as mediators of suicide attempt and use of crisis services. We will estimate direct and indirect effects in our longitudinal settings using our previously proposed GLMMs [51]. Specifically, we will test the effect of the intervention (risk model study group, yes/no) on behavioral health service engagement (yes/no within 7 and 14 days via path ‘*a’*) and the effect of behavioral health service engagement on suicide attempt outcome (yes/no within 90 and 180 days via path ‘*b*’). The residual effect of the intervention unaccounted for by behavioral health service engagement will be tested via path ‘*c*’. We will also test a separate path model of exposure to documented suicide prevention interventions and their impact on suicide attempt outcomes using the same modeling approach. These models will include both individual documented supportive outpatient interventions for suicide and multiple interventions bundled together; we will also repeat these analyses for crisis services outcomes.

We will address missing data using multiple imputation or inverse probability weighting, depending on the nature and extent of missingness. Additionally, if the proportion of missing data is substantial, we will conduct sensitivity analyses to assess its potential impact on our findings.

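### The alert-interaction mechanism analysis omits the model's own risk score, so predicted risk confounds the path from alert to suicide attempt

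*Protocol article*

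**What the plan says.** All of this is in the protocol article.

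- **Mechanism test.** After describing the mixed models for identification and recognition, Analysis plan for effectiveness outcomes says: "These models will also be used to test mediators/mechanisms". The same sentence gives lower suicide outcomes as the end of the causal chain. It continues: "Mechanisms include interaction with the alert and initiation of assessment, which starts the outpatient care pathway".
- **Model.** The exposure term is binary: "The model will include the intervention (yes/no) as an independent variable to assess its effect while accounting for clustering and potential confounders". The terms named are age, sex, race/ethnicity, clinic, phase and time, calendar month and frequency of visits. Neither the risk score nor the flag is among them.
- **Direct and indirect effects.** Later in the same section: "We will estimate direct and indirect effects in our longitudinal settings using our previously proposed GLMMs". The paths written out there are for service engagement and documented prevention interventions.
- **When an alert can exist.** Under Overview of study design, implementation starts when a clinic "transitions from usual care to running the risk model so clinicians can observe the risk indicator".
- **What triggers it.** Under Proposed care models, "the suicide risk model flags the clinician in the EHR to conduct additional suicide risk screening", on the basis of elevated estimated risk. Sample size and power analysis expects that "4–5% of patients will be identified as high risk and thus eligible for the intervention".

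**The concern.** Write A for the exposed period and M for interaction with the alert. M is zero in every control visit. In exposed visits it can be one only where the model has ranked the visit as high risk. If A and M enter one model for attempts without the score, two comparisons go wrong:

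- The M coefficient compares flagged visits with mostly unflagged ones. It picks up the risk that caused the flag.
- The A coefficient compares exposed visits, after some of the highest-risk ones have been moved into M, with all control visits. It looks protective.

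The direction needs only that the flag predicts attempts, which is the premise of the trial. At stake is the explanation of how the model works, and this would feed the implementation tool kit. Health systems could be told that acting on a suicide alert goes with more attempts, and that the rest of the programme has a benefit it does not have.

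**Working it through.** **The plan's own figure.** The article gives no figure for the mechanism analysis. Its event count reproduces: 0.006 × 395,000 = 2,370.

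**Inputs from the article.** Attempt rate p = 0.6% within 90 days; share flagged f = 4 to 5%; C-statistic 0.83 to 0.86 (Background).

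**Assumptions not in the article.** A binormal score; f, stated for patients, applied to visits; uptake u (share of flags acted on), at random among flagged visits; no intervention effect.

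**Closed form.**

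1. Separation of the score distributions: d = √2 × Φ⁻¹(C), giving 1.349 at C = 0.83 and 1.528 at C = 0.86.
2. The threshold t solves p × [1 − Φ(t − d)] + (1 − p) × [1 − Φ(t)] = f. Sensitivity is s = 1 − Φ(t − d).
3. Attempt rate in flagged visits: r₁ = p × s / f.
4. Attempt rate in exposed visits without alert interaction: r₀ = (p − u f r₁) / (1 − u f).
5. Alert OR = odds(r₁) / odds(r₀). Direct OR = odds(r₀) / odds(p).

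Example with C = 0.83, f = 5%, u = 1: t = 1.664 and s = 0.376. Then r₁ = 0.006 × 0.376 / 0.05 = 4.5% and r₀ = 0.006 × 0.624 / 0.95 = 0.394%. The alert OR is 12.0 and the direct OR 0.655.

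| C | f | r₁ | Alert OR, u = 100 / 50 / 30% | Direct OR, u = 100 / 50 / 30% |
|---|---|---|---|---|
| 0.83 | 4% | 5.05% | 12.8 / 10.4 / 9.7 | 0.69 / 0.85 / 0.91 |
| 0.83 | 5% | 4.52% | 12.0 / 9.4 / 8.7 | 0.66 / 0.83 / 0.90 |
| 0.86 | 4% | 6.03% | 17.1 / 13.0 / 11.9 | 0.62 / 0.82 / 0.89 |
| 0.86 | 5% | 5.33% | 16.0 / 11.7 / 10.6 | 0.58 / 0.80 / 0.88 |

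At full uptake r₀ is 0.35 to 0.42% against 0.60% in control visits: a false direct benefit of 1.8 to 2.5 attempts per 1000, offset by an equal false indirect harm. The true total is zero.

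**Simulated stepped wedge.** 51 clinics, three waves, four periods, 395,000 observations, C about 0.85, 4.5% flagged, no intervention effect. The logistic model had period and clinic terms, with clinics as fixed effects in place of the random effect. There were 44 to 100 replicates per setting.

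| Model | Uptake | Direct OR | Significant direct benefit | Alert OR | Significant alert harm |
|---|---|---|---|---|---|
| A + M | 100% | 0.63 | 100% | 14.4 | 100% |
| A + M | 70% | 0.75 | 96% | 12.0 | 100% |
| A + M | 30% | 0.89 | 31% | 10.2 | 100% |
| A + M + proxy correlated 0.7 with the score | 70% | 0.80 | 84% | 3.7 | 100% |

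At 70% uptake, three further checks:

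- **Total effect (A alone):** OR 0.99, rejected in 4% of runs.
- **A + M + flag computed in both periods:** direct OR 0.99, significant benefit in 2%; alert OR 1.00, rejected in 2%.
- **A + M + continuous score:** direct OR 0.99, significant benefit in 2%; alert OR 1.00, rejected in 6%.

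**The case against.** The strongest reply is that the faulted model is partly inferred. One sentence names alert interaction; no equation or population is given for it, and the paths written out for direct and indirect effects have other mediators. The abstract ties the primary outcome to visits at which the model identified the person, whereas Study measures and effectiveness outcomes uses all visits. If the mechanism analysis covered model-identified visits in both periods, the contrast between flagged and unflagged visits would not arise. The article also leaves room for unspecified confounders, and brings in diagnoses and prior attempts as moderators.

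Part of this stands: the a/b/c paths cannot be cited as fixing the alert model. But the text does send alert interaction through the stated models towards suicide outcomes, and it lists covariates without the score. Proxies reduce the bias without removing it, as the simulation shows.

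A reader might also infer more than the article supports:

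- **That a mediator absent under control is itself the error.** A component of an intervention is naturally absent under control. With the flag in the model and M retained, the bias disappears, so the fault is confounding by predicted risk.
- **That both false results are near certain.** This holds for the alert path at every uptake simulated. The false direct benefit was significant in only 31% of runs at 30% uptake.
- **That the effectiveness result is compromised.** The total effect does not condition on M and is unaffected.
- **That initiation of assessment has the same structural zero.** Assessments also take place in usual care.

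**Conclusion.** The point holds for the alert-interaction mechanism analysis. Under the models as described, predicted risk confounds the path from alert to attempt. With no intervention effect, the alert odds ratio is about 9 to 17 at 30 to 100% uptake. The residual direct odds ratio is 0.58 to 0.69 at full uptake, 0.80 to 0.85 at half and about 0.9 at 30%. False harm through the alert appears at every uptake examined; false direct benefit is reliably significant only at moderate to high uptake.

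The direction follows from the design. The sizes rest on the binormal score, on 4 to 5% applied per visit, on uptake at random among flagged visits, and on an all-visit analysis without the score. The primary analysis stands. This is a correction to a supporting analysis that should be made before the mechanism results are interpreted.

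**What to change.** Compute the model score retrospectively for control-period visits. Study measures and effectiveness outcomes implies that this is possible, since it plans to report, for usual care participants too, a recognition measure that uses model-estimated risk. Then do one of the following for alert interaction and initiation of assessment:

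- restrict the mechanism analysis to visits above the site's threshold in both exposed and control periods; or
- keep all visits and add the score or flag as a covariate.

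If control visits cannot be scored, report alert interaction only as a measure of use among flagged intervention visits, not as a mediator of attempts. State the chosen population and covariates in the plan.

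The cost is the scoring of control visits from data the sites already hold, and fewer visits if the analysis is restricted. Some confounding may remain in either version if clinicians act selectively among flagged patients, and the report should say so.

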### Kaiser Permanente Northwest (KPNW)

KPNW includes 10 behavioral health clinics serving approximately 50,000 patients annually, a behavioral health inpatient hospital, and a dedicated ZS implementation team. In 2007, KPNW began screening all patients attending outpatient behavioral health office visits using the PHQ9. Strategies expanded to include the C-SSRS in 2012, an EHR version of the C-SSRS in 2016 and a revision in 2018 making the data more accessible for research and quality improvement. Safety planning, means counseling, caring contacts, and cognitive behavioral therapy (CBT) are standard care.

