### Henry Ford Health (HFH)

HFH has four outpatient behavioral health clinics serving > 60,000 patients annually and four behavioral health inpatient hospitals. The department has a suicide prevention task force, which oversees implementation, evaluation, and quality improvement for the ZS Program, which have been implemented since 2001. Indeed, ZS was developed from the Perfect Depression Care [27–29] initiative at Henry Ford; this site has a long history of international leadership in suicide prevention. In 2018, HFH updated its ZS protocols, including use of universal screening along with suicide risk assessment, safety planning, caring contacts, care coordination, and a comprehensive means safety protocol. All psychotherapists are trained in CBT. The health system also implemented a dialectical behavioral therapy program for suicide prevention.

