### HealthPartners (HP)

HP is an integrated health care system with 39 behavioral health clinics serving approximately 58,000 patients annually. HP has used the PHQ9 since 2007. More recently, HP behavioral health and primary care leadership has been active in a statewide collaborative to implement ZS led by the Institute for Clinical Systems Improvement. This has included a roll-out of a depression express lane in HP’s EHR, including integration of the C-SSRS and safety planning. The MHRN suicide risk model was incorporated into HP’s health plan’s care management workflow in 2019 and into a pilot study of a clinical decision support tool for patients with opioid use disorder in eight primary care clinics in 2021 [30], but it has not previously been more widely implemented into behavioral health clinical care.

The three sites provide important variability in size, organizational structure, and degree of ZS implementation that will enrich outcome and covariate comparisons in the study.

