### Clinic randomization and eligibility

Sites will provide a list of behavioral health clinics to the lead analytical site (HFH). The goal is to randomize clinics into two or three waves each starting approximately three to six months apart with all waves eventually participating in the intervention (see Fig. 1). Randomization across sites will be conducted in SAS 9.4 with a simple randomization procedure (PROC SURVEYSELECT), to determine which clinics will enter the implementation period first.

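### Stratifying by health system does not test whether the effect differs between systems, and Henry Ford Health's stand-alone result would rest on four randomized clinics

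*Protocol article*

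**What the plan says.** The protocol article, under Analysis plan for effectiveness outcomes, states: "We will also stratify analyses by health system site". The same sentence names diagnoses and prior attempts as moderators to be tested, but gives health system stratification instead. The only site term mentioned later in that section is an adjustment covariate. The models are mixed models with a random clinic effect and fixed phase effects, reported as odds ratios or relative risks with 95% intervals. Nothing labels the per-system results descriptive.

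The systems differ greatly in number of clinics:
- "HFH has four outpatient behavioral health clinics serving" more than 60,000 patients a year.
- "KPNW includes 10 behavioral health clinics", with about 50,000 patients a year.
- "HP is an integrated health care system with 39 behavioral health clinics", with about 58,000 patients a year.

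On allocation, Clinic randomization and eligibility says: "The goal is to randomize clinics into two or three waves each starting approximately three to six months apart". Overview of study design says: "Implementation begins when each randomized clinic (stratified by site) transitions from usual care to running the risk model". The section on HealthPartners (HP) expects the sites' variability in size, structure and "degree of ZS implementation that will enrich outcome and covariate comparisons in the study".

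**The concern.** There are two separate problems.

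1. Fitting the model within each system does not answer whether the effect differs between systems. An interval that excludes 1 in one system and includes it in another is not evidence of a difference, yet three side-by-side results invite that reading.
2. The HFH fit has four randomized units. HFH reports the most patients of the three systems, about 36% (60,000 / 168,000, where 168,000 = 50,000 + 60,000 + 58,000), and has run its Zero Suicide program since 2001. A stand-alone effect or null result there would carry weight with readers while resting on little randomization and on a variance model that four clinics cannot check.

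**Working it through.** **Figures in the article.** Clinics: 10 + 4 + 39 = 53, which agrees with "We anticipate including > 50 clinics". Events: 395,000 x 0.006 = 2,370, as stated. The power statement covers the pooled trial only; no per-system figure is given.

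**What randomization alone can support at HFH.** Take wave sizes within the system as fixed, so that the smallest p is set by the number of equally likely allocations.
- Three waves, two clinics in one and one in each of the others: 4!/(2!1!1!) = 12 allocations; smallest p = 1/12 = 0.083.
- Two waves, 2/2: 4!/(2!2!) = 6. Swapping the waves mirrors the statistic, so the two-sided minimum is 2/6 = 0.33 (one-sided 1/6 = 0.167).
- Two waves, 1/3 or 3/1: 4 allocations; minimum 1/4 = 0.25.
- For comparison, Kaiser Permanente Northwest (KPNW) has 10!/(4!3!3!) = 4,200 or 10!/(5!5!) = 252 allocations, so the limit is specific to HFH.

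If instead each HFH clinic were assigned independently to one of three waves, there would be 3^4 = 81 assignments, 36 of them with every wave filled. The unconditional minimum would be 1/81 = 0.012 or 1/36 = 0.028. Given the realised wave sizes, the number is again at most 12.

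**What the model would report.** Null simulation of HFH alone: 36% of 395,000 = 142,200 patients over 4 clinics, split 2/1/1, with periods of 12/4.5/4.5/9 months; clinic and period effects fitted, no clinic-by-period term, nominal 5% model-based test. The split, the period lengths, the clinic-by-period SDs and the 20% outcome rate are assumptions. Each cell shows the rejection rate (%) in a run of 4,000 / in a repeat of 3,000.

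| Clinic-by-period SD | 0 | 5% | 10% | 15% |
|---|---|---|---|---|
| Attempts (0.6%) | 4.5 / 5.3 | 6.1 / 6.3 | 10.1 / 9.7 | 15.3 / 16.6 |
| Common outcome (20%) | 2.8 / 4 | 34 / 39 | 62 / 65 | 75 / 76 |

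A logistic version (5,000 patients per clinic-period, fixed clinic effects standing in for the random intercept, 0.6% rate) rejects 5.3%, 10.2%, 21.2% and 33.6% at log-odds SDs of 0, 0.1, 0.2 and 0.3. With a t reference on 3 df, the same fits reject 0.1%, 0.6%, 4.2% and 12.4%. The HFH result therefore depends heavily on the reference distribution and on an unknown variance.

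**Why the variance is hard to learn from HFH.** A 4.5-month cell holds 142,200 / 4 x 4.5/30 = 5,332 patients, or about 32 attempts. The sampling SD of its log rate is about 1/sqrt(32) = 0.18, larger than the 0.10-0.15 to be detected.

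**Is the inflation due to having four clinics?** No. For the 20% outcome the same cell has about 1,066 events and a sampling SD of sqrt(0.8/1,066) = 0.03, so omitted variation of 0.10 dominates whatever the number of clinics. Keeping clinics at HFH size and using 4, 10 and 39 of them gives 66%, 64% and 67% at SD 10%. For attempts at SD 15% it gives 14.5%, 15.5% and 14.4%. What matters is clinic size. Annual patients per clinic are about 60,000/4 = 15,000 at HFH, 50,000/10 = 5,000 at KPNW and 58,000/39 = 1,487 at HP, so HFH is the most exposed of the three.

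**The case against.** The strongest reply is that the article plans no randomization test, no per-system p-value and no per-system claim. Degrees of freedom, small-sample methods and the status of subgroup results may be settled in an analysis plan that is not shown. That is fair, and their absence is not the point here. What the article does fix is stratification for system beside moderator tests for other factors, and that choice leaves the between-system question unanswered. A small-sample correction elsewhere would improve calibration but would not add clinics.

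Three stronger readings are tempting and are not supported.
- A reader might infer that HFH cannot reach p < 0.05. The 0.083 minimum applies to a randomization test with fixed wave sizes. The article gives no within-site wave sizes and describes both site stratification and a simple procedure run across sites; independent assignment to three waves would take the unconditional minimum below 0.05.
- A reader might attribute the 62-75% rejection for common outcomes to having only four clinics. It comes from leaving out clinic-by-period variation in large clinics, at SDs the documents do not give.
- A reader might take the remark on site variability as a promise to test effect differences between systems. It promises comparisons in general terms only. The planned exploration of effect heterogeneity is between clinics.

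It is also true that an interaction model leaves HFH's own estimate resting on the same four clinics, especially if period effects are system-specific. The interaction term alone is therefore not a sufficient remedy.

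**Conclusion.** The concern holds in this limited form. Stratified fits do not test for a difference between systems, and a stand-alone HFH interval would have weak support from randomization. It would also be too narrow if clinic rates vary between periods. For attempts, the error rate is close to nominal with no such variation and roughly two to three times nominal at an assumed SD of 10-15%; common outcomes such as completed risk assessments are more exposed. These sizes rest on the assumed SDs, cell sizes and wave split, and on reading stratification as a separate fit in each system. This is a secondary analysis, but the wording should be changed before the data are analysed.

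**What to change.** - Replace the separate per-system fits with an intervention-by-system interaction in the pooled model, tested on 3 - 1 = 2 df.
- Include a clinic-by-period random effect, so that its variance is estimated from about 53 clinics instead of four (this assumes a similar variance across systems), and use a small-sample reference distribution.
- Report each system's estimate and interval from that model. Label HFH's as descriptive, with no stand-alone significance claim.
- State whether wave sizes are fixed within each system, so that the allocation scheme is unambiguous.

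The cost is some wording, two model terms (the interaction and the random effect) and the loss of per-system significance statements. Intervals will widen where clinic-by-period variation is present.
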